### Outcome measures

The initial research questions addressed in this study are “Does the educational intervention based on the I-Change model via mobile app affect CC preventive behaviors among Iranian women?”. To answer this main question, the following primary outcomes are expected:Determining and comparing the effects of an educational intervention designed based on the I-Change model via a mobile app knowledge related to CC prevention in women in the target and control groups before, immediately, and 3 months after the interventions.Determining and comparing the effects of an educational intervention designed based on the I-Change model via a mobile app on information factors related to CC prevention in women in the target and control groups before, immediately, and 3 months after the interventions.Determining and comparing the effects of an educational intervention designed based on the I-Change model via a mobile app motivation to CC prevention in women in the target and control groups before, immediately, and 3 months after the interventions.Determining and comparing the effects of an educational intervention designed based on the I-Change model via a mobile app predisposing factors to CC prevention in women in the target and control groups before, immediately, and 3 months after the interventions.Determining and comparing the effects of an educational intervention designed based on the I-Change model via a mobile app behavioral intention to CC prevention in women in the target and control groups before, immediately, and 3 months after the interventions.Determining and comparing the effects of an educational intervention designed based on the I-Change model via a mobile app action to prevent for CC prevention in women in the target and control groups before, immediately, and 3 months after the interventions.

Consequently, we expect the effect of our educational intervention on preventive action regarding CC among women. To assess the expected secondary outcomes, a self-reported assessment addressing preventive actions (using a condom, doing pap-test and genital examination) will be conducted.

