### Randomization

After informed consent and baseline data collection, participants in the randomized controlled trial will be randomly assigned to the intervention and control arms in a restricted randomized block design. A research identification number will be given to each woman. Then, the identified individuals who volunteered to participate in the study were randomly assigned to the experimental and control groups using a blocking method. Following simple randomization procedures, participants will be assigned to one of the three arms of the trial in a 1:1:1 ratio according to a computer-generated randomization schedule via https://www.sealedenvelope.com/simple-randomiser/v1/lists. The letter A will be considered for the intervention group1, the letter B will be considered for the intervention group2, and the letter C for the control group. The process of random allocation will be continued continuously until the sample size will be reached. Masking of participants and study staff is not possible due to the nature of the intervention (educational) and allocation ratio.

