### Sample size and power calculations

The sample size was determined by the primary objective (comparison of participation in the experiment and control groups, respectively) and women will be allocated in equal numbers to the three randomization groups. Following the study conducted [34], the sample size we require in the quantitative phase to provide sufficient power was calculated as 61 persons for each group. This sample size was calculated to be adequate at an alpha of 0.05 and a power of .80, to test for a difference between the groups. We considered a potential dropout rate of 15%. According to the formula below, we should start with a recruitment target of 70 participants in each group: $${n}_1={n}_2=\frac{\left({s}_1^2+{s}_2^2\right){\left({z}_{1- {\propto }\!\left/ \ {2}\right.}+{z}_{1-\beta}\right)}^2\ }{{\left(\mu {\mu}_2\right)}^{2.}}$$

In line with this approach, a total of 210 women aged 18–49 years will be recruited using the inclusion and exclusion criteria listed in Table 1. Participants will be allocated into three groups (the two intervention groups plus one control group).

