#### Phase 5: analysis of intervention outcomes

To ensure that the data is correctly entered, a double-entry of data will be performed by two different individuals. All data obtained from women will be entered into SPSS software. A code will be defined to identify missing data. The obtained data will be kept strictly confidential and will be stored with secured and restricted access; also, the signed consent will be kept locked. Follow-up data are received using the same questionnaires as used at baseline. The intervention will be evaluated based only on Pap smear completion 3 months after the enrollment and baseline survey. Data will be summarized with descriptive statistics (mean, median, standard deviation, percentiles for numerical variables, frequencies, and percentages for categorical variables). To determine the normality of data, Smirnov and Kolmogorov will be used. Determining the frequency of demographic information in both groups is analyzed using descriptive statistics templates. To analyze the quantitative variables, the independent *t*-test and paired *t*-test are analyzed. To compare the mean score, the quantitative (intra-group) variables of the two groups of the test and control groups before and after the intervention were used as independent samples. To compare the means, the quantitative (inter-group) variables were compared between the two groups of control and test before and after paired *t*-test intervention is used. In the case of non-normalization, the mean score of the quantitative (intra-group) variables in the two groups of the test and control groups is used before and after the intervention in Mann-Whitney. To compare the meanings, the quantitative variables (inter-group) were used in both control and test groups before and after the Wilcoxon test. To determine the relationship between the underlying and dependent variables in the case of normal, the Pierson correlation test is used and the Spearman correlation test will be used to determine the relationship between the underlying and dependent variables in the case of normal. To analyze the qualitative variables, a chi-square test is used to analyze the qualitative variables. The significance level in this study is considered to be 0.5. The information obtained will be used by the related statistical software, including SPSS version 23.

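### The planned between-arm tests of the I-Change construct scores ignore the baseline score, which costs precision and control of chance baseline imbalance

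*Protocol article*

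**What the plan says.** Under *Outcome measures*, the Protocol article lists six I-Change constructs as primary outcomes: knowledge, information factors, motivation, predisposing factors, behavioural intention and action. Each is to be compared between groups at three times, for example "motivation to CC prevention in women in the target and control groups before, immediately, and 3 months after the interventions".

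Under *Randomization*, the baseline measurement precedes allocation: "After informed consent and baseline data collection, participants in the randomized controlled trial will be randomly assigned to the intervention and control arms".

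Under *Phase 5: analysis of intervention outcomes*, the instrument is the same at each time: "Follow-up data are received using the same questionnaires as used at baseline". The same section fixes the tests: "To analyze the quantitative variables, the independent *t*-test and paired *t*-test are analyzed". If the data are not normal, Mann-Whitney and Wilcoxon tests replace them. The only other tests named are correlations and chi-square. The section also states that the intervention will be judged solely on Pap smear completion at 3 months.

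Under *Sample size and power calculations*, the article reports 61 per group, raised to 70 for 15% dropout: "This sample size was calculated to be adequate at an alpha of 0.05 and a power of .80". The printed formula is the unadjusted comparison of two means.

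**The concern.** Each woman should have a pre-randomisation value of every construct score on the same instrument as the follow-up value. That baseline score is normally a strong predictor of the follow-up score, yet no planned between-arm test uses it as a covariate.

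This has three consequences:

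- Variation between women that baseline would explain stays in the error term, so standard errors are larger than they need be.
- If the arms differ by chance at baseline, part of that difference carries into the follow-up contrast. Testing the groups separately before and after can reveal such a difference but cannot correct for it.
- A paired or Wilcoxon test within one arm says whether that arm changed. It does not estimate the difference between arms, which is the trial's question.

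The article names its tests one by one, including the fallback for non-normal data. This is therefore a stated choice, not a detail left to a fuller document.

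**Working it through.** **1. Does any planned test use baseline?** The wording in *Phase 5: analysis of intervention outcomes* is garbled: the intra-group label is attached to independent-samples tests and the inter-group label to paired tests. There are two readings.

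- If the labels are swapped, the between-arm test is an independent t-test (or Mann-Whitney) on scores at one time, and the paired test is within arm.
- If the labels are taken literally, the tests do not match the comparisons they are assigned to.

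Under either reading there is no ANCOVA, baseline-adjusted regression, mixed model or between-arm comparison of change.

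**2. The plan's own figure.** Inputs from *Sample size and power calculations*: n = 61 per group, alpha 0.05, power 0.80, two-sided because the formula uses z(1−α/2). The article gives no means or SDs, so 61 cannot be reproduced. It can only be solved backwards:

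d = (1.960 + 0.842) × √(2/61) = 0.507

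This is the standardised difference for which 61 per group gives 80% power in an unadjusted test of two arms. It is not an effect size stated for any construct. The analysis section says "The significance level in this study is considered to be 0.5", which conflicts with the 0.05 of the sample-size section; 0.05 is used here.

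**3. Effect of adjustment on power.** Assumption: rho is not given, so a range of 0.3 to 0.7 is shown. With adjustment the residual SD is SD × √(1 − rho²), so for one pairwise contrast at 61 per group:

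power = Φ(2.80/√(1 − rho²) − 1.96)

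| rho (assumed) | Variance reduction (rho²) | Power, unadjusted | Power, adjusted |
|---|---|---|---|
| 0.3 | 9% | 80% | 83.6% |
| 0.5 | 25% | 80% | 89.9% |
| 0.7 | 49% | 80% | 97.5% |

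The t distribution in place of the normal changes these by about 1 point or less (79.4% unadjusted and 89.4% adjusted at rho = 0.5).

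**4. Effect of a chance baseline imbalance.** With 61 per group, the standard error of a baseline difference is √(2/61) = 0.181 SD. A difference of 1.96 standard errors is 0.355 SD. The expected shift in the unadjusted follow-up difference is rho × 0.355 SD. Given that imbalance and no true effect, the unadjusted test statistic has mean 1.96 × rho and variance 1 − rho². The chance of a false positive is then:

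1 − Φ((1.96 − 1.96 rho)/√(1 − rho²)) + Φ((−1.96 − 1.96 rho)/√(1 − rho²))

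| rho (assumed) | Shift (SD) | Share of d = 0.507 | Type I error given this imbalance |
|---|---|---|---|
| 0.3 | 0.11 | 21% | 7.9% |
| 0.5 | 0.18 | 35% | 12.9% |
| 0.7 | 0.25 | 49% | 20.5% |

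When the arms are exactly balanced at baseline, the same formula with zero imbalance gives 4.0%, 2.4% and 0.6%. Over all randomisations the error averages 5%.

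**The case against.** The strongest reply is that nothing here is an error. Between randomised arms the unadjusted comparison is unbiased and keeps its type I error over all randomisations. That stands. A reader might infer from the second table that the planned test is invalid or biased; the table is conditional on an unlucky allocation and does not show that. Nor does a baseline difference pass in full into the result: only the part scaled by rho does.

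The second reply concerns the figures. A reader might infer that this trial has 80% power for the construct scores and would reach 90%, or could manage with fewer women. The documents do not support this. The sample-size section describes its objective as a comparison of participation, takes its inputs from a cited study and states no effect size. The questionnaire is still to be developed in Phase 3, so nothing favours one value of rho. At 0.3 the gain is only 3.6 points.

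Third, the analysis section says evaluation rests on Pap smear completion alone. If that sentence governs, the construct scores are supporting outcomes and the power figures do not carry over to the binary endpoint. This limits the point but does not remove it: *Outcome measures* still calls the scores primary, and the analysis section still specifies tests for them.

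Fourth, not every listed outcome need be continuous. Action may be recorded as condom use, Pap test and genital examination, and the article does not say that these form a score.

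**Conclusion.** The point holds for the constructs scored as continuous variables. The stated analysis leaves out a pre-randomisation measure of the same outcome, and so gives up precision and control of chance imbalance. It is an avoidable inefficiency that should be corrected, not a flaw that invalidates the comparison.

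The size depends on a correlation the article does not give. For a hypothetical outcome with 80% unadjusted power at 61 per group, two-sided alpha 0.05 and one pairwise contrast, power would be about 84% to 97% for rho between 0.3 and 0.7. These are illustrations, not estimates of this trial's power. Separately, the list of primary outcomes and the statement that only Pap smear completion counts contradict each other and must be reconciled.

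**What to change.** In *Phase 5: analysis of intervention outcomes*:

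- For each construct scored as a continuous variable, make the between-arm analysis a linear model (ANCOVA) of the follow-up score, immediate and 3-month, on a three-level arm factor and the baseline score of the same construct. Alternatively, use a mixed model over both follow-ups with baseline as covariate. The two can differ when follow-up is incomplete, and 15% dropout is allowed for, so name one in advance.
- Report adjusted mean differences between arms with 95% confidence intervals.
- Keep the within-arm before/after tests as descriptive only.
- If action is binary, use a model suited to a binary outcome with its baseline value as covariate.
- State whether the construct scores or Pap smear completion are the basis of evaluation, and bring *Outcome measures* into line.

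The cost is a change of wording before the analysis. The baseline data are already planned, so no extra women, visits or measurements are needed. The downside is one degree of freedom and an adjusted rather than raw mean difference.

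### The Phase 5 analysis text assigns paired tests to between-arm comparisons and unpaired tests to before/after comparisons; probably a drafting swap, but wrong as written

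*Protocol article*

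**What the plan says.** The Phase 5 section (Statistical methods and analysis) opens its treatment of quantitative variables by naming both the independent and the paired t-test. It then assigns a test to each type of comparison:

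- Within group, normal data: "the quantitative (intra-group) variables of the two groups of the test and control groups before and after the intervention were used as independent samples".
- Between groups, normal data: "the quantitative (inter-group) variables were compared between the two groups of control and test before and after paired", after which the sentence names the t-test.
- Within group, non-normal data: "intra-group) variables in the two groups of the test and control groups is used before and after the intervention in Mann-Whitney".
- Between groups, non-normal data: "the quantitative variables (inter-group) were used in both control and test groups before and after the Wilcoxon test".

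Two other statements fix the structure of the data. Under Randomization, "participants will be assigned to one of the three arms of the trial in a 1:1:1 ratio", with no matching of women across arms. In the Phase 5 section, "Follow-up data are received using the same questionnaires as used at baseline". The sample-size section prints the formula for comparing two independent means.

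**The concern.** Women in different arms are different people, randomised individually, so their scores are independent. A woman's baseline and follow-up scores come from the same person on the same questionnaire, so they are paired. The text gives each structure the test that belongs to the other, in both the parametric and the non-parametric rule.

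The Outcome measures section lists six primary outcomes, mostly I-Change constructs such as knowledge, motivation and intention, to be compared between target and control groups. The four sentences above are the only rule the article gives for analysing such scores. If they were carried into the analysis literally, the randomised comparison of those scores would depend on how rows happened to be lined up, and the before/after tests would use the wrong standard error.

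**Working it through.** **Design against assigned test**

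| Comparison | Data structure | Test that fits | Test assigned |
|---|---|---|---|
| Within arm, normal | same women, two times | paired t | independent samples |
| Between arms, normal | different women, unmatched | independent t | paired t |
| Within arm, non-normal | same women, two times | Wilcoxon signed-rank | Mann-Whitney |
| Between arms, non-normal | different women, unmatched | Mann-Whitney | Wilcoxon (type not stated) |

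**The plan's own sample size.** It gives 61 per group at alpha 0.05 and power 0.80, and 70 after allowing for 15% dropout. The 70 is reproduced as 61 × 1.15 = 70.15 (dividing by 0.85 would give 71.8). The 61 cannot be rebuilt because no means or SDs are given. Solving the printed formula for the standardised difference gives √2 × (1.96 + 0.84)/√61 = 0.507 SD. That formula assumes two independent groups, so it agrees with an independent between-arm test and not with a paired one.

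**Within arm, as written.** Take n = 61 and assume a 0.3 SD change, equal SDs at both times and a baseline/follow-up correlation ρ. The documents give neither the change nor ρ.

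- Paired test: the SD of the change is √(2(1 − ρ)), which is 1 at ρ = 0.5. The expected statistic is 0.3 × √61 = 2.34, so power = P(Z > 1.96 − 2.34), about 0.65. Simulation of the t-test gives 0.64.
- Unpaired test on the same data: the expected statistic is 0.3 × √(61/2) = 1.66. Its true SD is √(1 − ρ) = 0.707 rather than 1. Power = P(Z > (1.96 − 1.66)/0.707), about 0.33; simulation gives 0.33.
- Type I error of the unpaired test at ρ = 0.5: 2 × P(Z > 1.96/0.707), about 0.006 by the normal approximation and 0.007 by simulation.

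Simulated values over a range of ρ (20,000 runs, two-sided 0.05):

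| ρ | Type I, unpaired | Type I, paired | Power, unpaired | Power, paired |
|---|---|---|---|---|
| 0.3 | 0.019 | 0.051 | 0.35 | 0.49 |
| 0.5 | 0.007 | 0.050 | 0.33 | 0.64 |
| 0.7 | 0.0005 | 0.049 | 0.29 | 0.85 |

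**Between arms, as written.** A paired test needs equal numbers and a rule for pairing; the design supplies no pairing rule. With 15% dropout, 70 × 0.85 = 59.5 women per arm are expected to remain, and the arms need not lose the same number. If equal arms of 61 are paired at random:

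- Type I error is 0.047 for the paired t-test (independent t: 0.048) and 0.044 for the signed-rank test.
- Power at 0.507 SD is 0.79 paired and 0.80 independent.
- In one simulated data set with an independent-test p of 0.034, re-pairing the same scores 5,000 times gave paired p-values from 0.016 to 0.061 (central 95%). The same data can therefore fall on either side of 0.05.
- If both arms happened to be sorted by score before pairing, the rejection rate with no true difference was 0.76.

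**The case against.** The strongest reply is that this is a labelling slip and not a choice of method. With the *intra-group* and *inter-group* labels removed, three of the four sentences make sense: independent samples and Mann-Whitney for test against control, and Wilcoxon for before against after. Only the paired t-test sentence also speaks of comparing between the two groups, and its wording is garbled. The sample-size formula points the same way. This explanation is probably right. It does not remove the error, because the labels are in the text, they are wrong in both rules, and nothing elsewhere corrects them. Nor is it detail that an article leaves to a fuller document: the assignments are stated.

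It is also fair that *Wilcoxon* is not specified. Read as the rank-sum test it would suit a between-arm comparison; beside Mann-Whitney, signed-rank is the natural reading. The other three assignments are reversed either way.

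Three stronger conclusions that a reader might draw are not supported:

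- *Every continuous comparison would be invalid, with inflated false positives.* The within-arm test errs on the conservative side, and random pairing of equal arms keeps type I error near nominal. Marked inflation appeared only when both arms were sorted by score.
- *Efficacy will be claimed from uncontrolled before/after change.* The Phase 5 section does not say so, and the Outcome measures section frames the outcomes as comparisons of target and control groups.
- *The whole trial result is affected.* The same section says that the intervention is evaluated on Pap smear completion alone. That is a binary outcome falling under the chi-square sentence, which this error does not touch.

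**Conclusion.** The point holds as an error in the written rule, most likely a drafting swap. It affects the questionnaire-score outcomes listed under Outcome measures, not the binary Pap smear outcome.

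Taken literally, the between-arm comparison of scores has no defined pairing. It cannot use all women when arm sizes differ, and with equal arms it yields a p-value that depends on row order. The within-arm comparison loses power, about 33% against 64%, and has a type I error of about 0.007. Those within-arm figures rest on an assumed 0.3 SD change and a correlation of 0.5; across correlations of 0.3 to 0.7 the loss runs from 0.49 down to 0.35, to 0.85 down to 0.29. The mismatch between test and design needs no assumption. The text should be corrected before analysis.

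**What to change.** In the Phase 5 analysis section:

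1. Assign the independent t-test (or Mann-Whitney, if a rank test is kept) to comparisons between arms.
2. Assign the paired t-test (or Wilcoxon, named as signed-rank) to before/after comparisons within an arm, and label these descriptive.
3. State that efficacy conclusions rest on the between-arm comparisons.

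This is a change of wording only. It needs no new data and leaves the sample size as it is, because the printed formula is already the one for independent groups. Exchanging the assignments corrects the mismatch but does not by itself say how two-group tests will cover three arms and three time points. A baseline-adjusted between-arm model (ANCOVA or a mixed model) could do that if the team is revising the paragraph anyway.

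### The only test named for categorical outcomes is an unadjusted chi-square; it is valid, but it leaves unused the questionnaire answers taken before randomisation and so gives up some precision and protection against chance imbalance

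*Protocol article*

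**What the plan says.** In the Protocol article, the section on Phase 5 analysis lists its tests one by one: t-tests, Mann-Whitney and Wilcoxon for scores, correlations, and for categorical data this: "To analyze the qualitative variables, a chi-square test is used to analyze the qualitative variables". No covariate or stratum is attached to it.

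The same section says "Follow-up data are received using the same questionnaires as used at baseline". The Randomization section puts the baseline assessment first: "After informed consent and baseline data collection, participants in the randomized controlled trial will be randomly assigned". Pre-randomisation answers from the follow-up instrument should therefore exist.

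The outcomes concerned appear in two places. Under Outcome measures, as secondary outcomes, "a self-reported assessment addressing preventive actions (using a condom, doing pap-test and genital examination) will be conducted". In the Phase 5 analysis, "The intervention will be evaluated based only on Pap smear completion 3 months after the enrollment and baseline survey".

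**The concern.** A woman's behaviour before the trial may predict her behaviour 3 months later. Condom users may tend to remain users, and a woman screened recently may be less likely to be screened again within 3 months. For scores the plan at least includes before-after tests. For categorical outcomes the named test compares the arms without reference to where each woman started.

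Two things are at stake. If baseline status is prognostic, a comparison that conditions on it has more power at the same sample size. And if chance gives one arm more women who already practise the behaviour, the crude difference carries that imbalance. The randomisation is blocked, but no stratification by earlier behaviour is stated.

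**Working it through.** **Inputs from the article.** The required size "was calculated as 61 persons for each group", described as "adequate at an alpha of 0.05 and a power of .80, to test for a difference between the groups"; 15% dropout; 70 recruited per arm; 1:1:1 allocation. The Background cites Pap participation in Iran of 27.1%, 50% and 58.6%, and the Discussion says that more than 40% of eligible women do not follow screening guidelines. All calculations use two-sided 0.05. The analysis section prints a different level ("The significance level in this study is considered to be 0.5"), which is a separate inconsistency.

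**The plan's own figure.** The formula is for two means: n = 2(1.960 + 0.842)²/d² = 15.70/d². No means or SDs are given, so 61 cannot be rebuilt. Solved backwards, d = √(15.70/61) = 0.51. For dropout, 61 × 1.15 = 70.15 matches 70, and 61/0.85 gives 72. I take 61 evaluable women per arm.

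**What 61 per arm can detect on a yes/no outcome.** At 80% power the detectable difference is about 17 points from a control rate of 5%, 20 from 10%, 25 from 27.1%, 24 from 50% and 23 from 58.6%. There is little power to spare.

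**How often baseline differs by chance.** The SD of the difference in baseline prevalence b between two arms is √(2b(1−b)/61): 0.0905 at b = 50% and 0.0805 at 27.1%. Since 6/61 is 9.8%, a gap of 10 points means at least 7 women. With a continuity correction, z = (6.5/61)/0.0905 = 1.18, or about 24%; at 27.1%, z = 1.32, or about 19%. Simulation gave 18 to 24%.

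**How much of that reaches the outcome.** The outcome rates of women with and without the behaviour at baseline differ by φ√[p(1−p)/(b(1−b))], where p is the outcome rate and φ the baseline-outcome correlation. With p = 27.1%, b = 50% and φ = 0.3 this is 0.3 × √(0.1976/0.25) = 0.267. A 10-point imbalance then shifts the crude difference by 2.7 points.

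**Simulation.** Two arms of 61, 20,000 runs per scenario. Assumed: baseline prevalence 27.1, 50 or 58.6%; control rate 10, 27.1 or 50%; the difference that gives chi-square about 80% power; φ from 0 upwards where attainable. The comparison is chi-square against a Mantel-Haenszel test stratified by baseline status.

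| φ | Change in power from stratifying (points) | Chi-square false positives when intervention arm is favoured by ≥10 points at baseline |
|---|---|---|
| 0 | −0.6 to −0.3 | about 5–6% |
| 0.2 | +0.5 to +2.5 | 6–7% |
| 0.3 | +2.5 to +7 | 6–9% |
| 0.5 | +7 to +16 | 10–13% |

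Under the same imbalance the stratified test stays at about 4 to 5.5%. Averaged over all randomisations, chi-square is at about 5 to 6%.

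A rerun (100,000 runs) matched the power column when the effect was a common odds ratio across baseline strata. With the effect set instead as a constant risk difference, the gains were +0.5 to +1.4 points at 0.2, +1.7 to +3.9 at 0.3 and +6 to +11.5 at 0.5. The upper ends of the table therefore depend on how the effect is spread over the strata.

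**Pap completion, assuming 60% up to date at baseline.** Power went from 50% to 54% at 5% v 16%, and from 46% to 51% at 9% v 21%. Low rates cap the correlation. At a 5% control rate, even if no up-to-date woman repeats the test, the strata are 12.5% and 0%, and φ is at most 0.125 × √(0.24/0.0475) = 0.28 in size. In that extreme the rerun gave 53% to 60% at 5% v 16% and 46% to 59% at 9% v 21%; with baseline unrelated there was no gain.

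**The proposed interval.** A Mantel-Haenszel risk difference with the Sato variance rejected a true null in 4.7 to 5.6% of the rerun's trials, including a Pap rate of 5%.

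**The case against.** The strongest reply is that nothing is wrong: an unadjusted comparison of randomised arms is valid, chance imbalance is already counted in its error rate, and covariates are often left to an analysis plan. The first two parts stand in full. The third stands only in part, because the article does not leave the test open. It names one, and that one is unadjusted.

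Three further limits stand. A baseline Pap item is an inference: the tool is still to be built in Phase 3 and the schedule table is not shown. Earlier testing is also a different variable from completion within 3 months, so it helps only as far as it is prognostic. And the article does not say that condom use or genital examination will be scored yes/no; if they become scores, the rules for scores apply.

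A reader might infer three stronger things that the document does not support.

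- That the chi-square inflates false positives. It does so only conditionally on an unfavourable imbalance, not overall.
- That the test governing the trial's sole outcome is at fault. The Phase 5 analysis rests the evaluation on Pap completion alone, but Outcome measures lists six I-Change outcomes as primary and the self-reported actions as secondary.
- That about 20 points of power are at stake. A condom-use scenario (40% at baseline, 40% v 57% at follow-up, correlation 0.75) does move from 49% to 69%. But with 40% and 57% the correlation cannot exceed √(0.40 × 0.43/(0.60 × 0.57)) = 0.71, so 0.75 cannot hold in the intervention arm.

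**Conclusion.** The point holds as a matter of efficiency, not validity. The plan fixes an unadjusted test where a baseline measure from the same questionnaire should be available. If baseline status is unrelated to the outcome, stratifying costs about half a point of power. At correlations of 0.3 to 0.5 it gains about 2.5 to 16 points, with the upper part of that range tied to a common odds ratio. For Pap completion a few points is the likely size. Stratifying also removes the conditional excess of false positives in the roughly one in five pairwise comparisons with a baseline gap of 10 points or more.

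All of this rests on assumed rates and correlations, since the article gives none for this population, and on 61 evaluable women per arm. Whether Pap completion is the sole or a secondary outcome must be reconciled separately; this point applies either way.

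**What to change.** Prespecify, for each preventive action scored yes/no at 3 months and each pairwise arm comparison, a Mantel-Haenszel risk difference with 95% CI, stratified by the woman's baseline status on that same behaviour. For Pap testing, the stratum is previous testing as recorded in the baseline questionnaire, with its categories defined in advance. Keep the chi-square as a sensitivity analysis and for descriptive tables.

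One fixed method is better here than logistic regression with a fallback. Events may be few (at 5% v 16%, about 61 × 0.21 = 13 over two arms), and a stratum without events would make the logistic model separate. A rule to switch when events are few would let the method be chosen after the data are seen.

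The cost is a sentence in the analysis section, a check that the questionnaire contains the baseline items, slightly more analysis work, and a negligible loss of power if baseline status turns out not to be prognostic. No additional participants are needed, and no new data if the items are there.

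### The analysis section sets the significance level at 0.5, while the sample size rests on 0.05; as written, half of all true-null tests would be declared significant.

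*Protocol article*

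**What the plan says.** The protocol article gives a significance level in two places.

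- **Sample size and power calculations:** "This sample size was calculated to be adequate at an alpha of 0.05 and a power of .80". The evaluable number "was calculated as 61 persons for each group", and the recruitment target is 70 per group, 210 in all. The section does not say in words that the test is two-sided, but its formula takes the normal quantile at 1 − α/2.
- **Phase 5: analysis of intervention outcomes:** after listing t-tests, Mann-Whitney and Wilcoxon tests, correlations and chi-square tests, the section ends with "The significance level in this study is considered to be 0.5".

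The second sentence is the only one that sets a level for the tests that will be run. No other part of the article corrects, qualifies or explains the 0.5.

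**The concern.** A significance level is the rule by which a trial calls a result positive. A level of 0.5 is no evidential standard: a p-value of 0.4 would meet it, and with no effect at all each test would be positive as often as a coin falls heads.

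The level also has to match the one used for planning. The stated 80% power is power at a 5% type I error. If the analysis used 0.5, the sizing and analysis sections would describe two different trials.

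A clear pre-specified error rate matters more than usual here. The Randomization section says that masking is not possible, and the Limitation section acknowledges self-reported measures and likely bias. The Discussion says that a positive result may make the app strategy an important tool against the disease, so the rule for a positive result must be right.

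**Working it through.** **Inputs**

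| Input | Value | Source |
|---|---|---|
| α, analysis | 0.5 | Phase 5: analysis of intervention outcomes |
| α, planning | 0.05 | Sample size and power calculations |
| Power | 0.80 | same section |
| Sidedness | two-sided, inferred from z at 1 − α/2 | formula in the same section |
| Evaluable n per group | 61 | same section |
| Means and SDs | not given; a cited study is named | same section |
| Listed primary outcomes | 6 | Outcome measures |

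**1. The plan's own figure.** The 61 per group cannot be reproduced directly, because no means or SDs are given. It can be solved backwards for the standardized difference d at two-sided 0.05 and 80% power:

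d = √[2(z₀.₉₇₅ + z₀.₈₀)² / n] = √[2(1.960 + 0.842)² / 61] = 0.507

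This is only the effect size that 61 implies. A check with rounded values gives 61 per group at d = 0.51 and 63 at d = 0.50. The present point does not depend on it, because it rests on the two stated levels alone.

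**2. Critical values.** The two-sided critical |z| is z at 1 − α/2.

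- α = 0.05: z₀.₉₇₅ = 1.960
- α = 0.5: z₀.₇₅ = 0.674

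With 61 per group, the standard error of a standardized mean difference is √(2/61) = 0.181. The smallest observed difference called significant is therefore 1.960 × 0.181 = 0.355 SD at 0.05, but only 0.674 × 0.181 = 0.122 SD at 0.5.

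**3. Error rate per test.** By definition it is 5% and 50%. A simulation of 20,000 null trials with 61 per group, analysed by the two-sample t-test, gave 4.9% at 0.05 and 50.05% at 0.5.

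**4. Several outcomes, as an illustration of scale.** Assume six tests, one per listed primary outcome, and no true effect.

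- Expected number of false positives: 6 × 0.5 = 3, against 6 × 0.05 = 0.3. This needs no independence.
- Chance of at least one, if the tests are independent: 1 − 0.5⁶ = 98.4%, against 1 − 0.95⁶ = 26.5%.

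**5. Link to the sample size.** With d = 0.507:

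- n per group for 80% power at α = 0.5: 2(0.674 + 0.842)² / 0.507² = 17.9, so 18, against the planned 61.
- Power of 61 per group at α = 0.5: d√(n/2) = 2.80, and Φ(2.80 − 0.674) = 98%, against 80% at 0.05.

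A trial meant to be tested at 0.5 would not have been sized at 61 per group for this effect. The sample size therefore belongs with 0.05.

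**The case against.** The strongest reply is that this is a dropped zero and not a choice of method. The intended value can be read from the sample size section, the sample size does not use the 0.5, and the same analysis paragraph has other drafting slips. On this view the practical harm is small, because nobody is likely to test at 0.5. The typing-error reading stands: nothing suggests that the investigators mean to use 0.5. It does not remove the defect, because the misprint falls in the one sentence that fixes the level for the analysis, and readers will judge the reported results against the published protocol.

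A second objection concerns the six-test figures. The outcomes are measured at several time points in three arms, so there may be more than six tests. The analysis section also says that evaluation rests on Pap smear completion alone, which would mean one outcome. Scores from one questionnaire in the same women are probably correlated. All of this is fair, so the 98.4% shows scale only. The 26.5% that remains at 0.05 is a separate matter of multiplicity, which this correction does not resolve. The contrast of 50% with 5% per test needs none of these assumptions, and it would hold equally for a single test of Pap smear completion.

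A digit lost when the text was read from the PDF is possible but unlikely: the sentence is complete running text, and the 0.05 in the sample size section came through intact.

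**Conclusion.** The concern holds. The only decision threshold stated for the trial's tests contradicts the level used for the sample size and is ten times as large. Taken literally, it gives a 50% false-positive rate for every true-null test where 5% was planned, and this follows from the two stated levels alone. The expected 3 false positives in 6 also assume one comparison per listed primary outcome and no true effect; the 98.4% further assumes independence. The implied standardized difference of 0.507 is back-solved, not taken from the document.

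The finding is that the printed figure is wrong, not that anyone intends to test at 0.5. It must be corrected, because it governs every comparison in the randomized phase.

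**What to change.** In the Phase 5 analysis section, replace 0.5 with a two-sided significance level of 0.05. The value matches the sample size section, and two-sidedness matches its formula; stating it in words removes the need to infer it. The sponsor should confirm that 0.05 was intended and that any separate analysis plan carries the same level.

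Reporting 95% confidence intervals for the between-arm differences would sit well with this level, but it is a secondary suggestion and the correction does not depend on it.

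The cost is one sentence in the protocol. Sample size, recruitment and data collection do not change.
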